#### Definition of secondary outcomes

The secondary outcomes include the time from the start of remimazolam infusion to MOAA/S zero, total induction dose of remimazolam tosylate when MOAA/S reaches zero, the BIS value and hemodynamic variables (HR, BP) at the baseline, MOAA/S zero and 1 min after intubation, adverse events during induction (such as injection pain, hiccup, bucking…), the dose of remifentanil, the BIS value during maintenance, and the total time stay in PACU.

### Safety management and adverse event

Researchers will make sure that the adverse event response team is on standby throughout the process. An adverse event refers to any untoward medical occurrence which happens during the trial. Adverse events include but are not limited to respiratory depression and cardiocirculatory instability. All adverse events will be treated immediately. For instance, if spontaneous respiration is insufficient during induction in obese subjects (SpO_2_ < 92%), auxiliary mask ventilation with an oropharyngeal airway will be given to the patients. Cardiovascular events should be handled promptly, with 6–12 mg ephedrine given if the patient’s systolic blood pressure is below 80 mmHg and 5 mg atropine given if the patient’s heart rate is below 45 bpm. The type of adverse event, likely cause, and treatment will be documented and discussed in data monitoring committee (DMC) meetings. If an adverse event occurs, the research team will afford free medical treatment and necessary follow-up.

### Data collection

Before surgery, general information (age, gender, height, TBW, BMI, LBW, IBW, ASA status, Mallampati score) and the surgical methods of the patients are investigated, and indexes such as albumin, alanine aminotransferase (ALT), and aspartate aminotransferase (AST) are recorded. Baseline BIS, HR, SBP, DBP, and MAP are recorded before induction (-t_1_). During induction, BIS and the hemodynamic profiles are recorded at the following time points: MOAA/S 0 (t_1_), before airway security (t_2_), 1 min after airway security (t_3_), beginning of operation (t_4_), the end of operation (t_5_), discharging from PACU (t_6_). The minimum SpO_2_ during induction (from administration to 5 min after intubation) will be recorded. Time from the start of administration of the remimazolam tosylate to MOAA/S 0, time from the end of administration to extubation, and time from the end of administration to discharge from the PACU are also recorded.

### Data management

Before the initiation of the study, electronic case report forms (CRFs) will be established with password-protected access. Each enrolled patient will be assigned an identification number. Original data will be collected on the case report forms (CRFs) by an anesthesiologist assistant blinded to the group allocation. We will indicate a coordinator to ensure the integrity of data collection and timely completion of the CRFs.

Two researchers will independently enter the data from CRFs into the database, which will be created using Microsoft Excel 2019 (Microsoft, USA). Consistency between the two entries will be tested. Patient data will be coded and kept confidential.

### Trial management and data monitoring

The compositions of the trial management group (TMG) include the principal investigators, research members, and the trial statistician team. The members of TMG will meet monthly to ensure that the progress of the study is conducted according to protocol, planned timelines, and budget. A semi-annual audit will be conducted by an independent clinical research expert from Clinical Research Unit of Eye & ENT Hospital of Fudan University, to ensure that the protocol is followed, there is no issue with the informed consent procedure, and record keeping is accurate.

The quality of data will be monitored quarterly by the data monitoring committee (DMC), which is composed of statisticians and representatives from the Ethics Committee and Clinical Research Unit of Eye & ENT Hospital, Fudan University. The members of the DMC are independent of the sponsors. After the data collection is completed, the researchers will be granted full access to the dataset.

### Participant timeline

The participant timeline is shown in Fig. 2.

### Sample size calculation

Although there was no previous study that demonstrated the optimum induction dose of remimazolam tosylate in obese patients. The sample size calculation is based on the ability to detect a difference of approximately 0.1 mg/kg between groups in the dose per kilogram of remimazolam tosylate. This is based on the studies which describe a clinically important difference of 0.12 with a standard deviation of 0.08 of the mean cumulative doses of remimazolam induction to reach LOC between 6 mg/kg/h and 12 mg/kg/h groups [23]. Based on these parameters, we calculated a sample size of 20 subjects per group with a power of 90%, alpha 0.025, and a 20% dropout rate.

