### Assignment of interventions: randomization and allocation

Forty obese patients are randomly allocated in a 1:1 ratio to either the TBW group or the LBW group after they sign the informed consent form. An independent statistician who was not directly involved with the study randomly allocated the obese patients into the TBW or LBW group according to a computer-generated randomization scheme. Patient assignments will be placed in sequentially numbered, opaque, sealed envelopes. The randomization scheme is kept inaccessible throughout the study period.

After the obese subject enters the operation room, the research nurse, who does not participate in anesthesia, will open the sealed envelope for random numbers, calculate, and set the infusion speed according to the group information.

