### Statistical analysis

#### Statistical analysis for primary and secondary outcomes

Baseline clinical and demographic characteristics will be summarized and reported using descriptive statistics. Categorical variables will be reported as numbers and percentages and will be compared using the chi-square test or Fisher’s exact test, as appropriate. The Shapiro-Wilks test will be used to first verify the normality of the continuous variables and will be reported as means and standard deviations or as medians and interquartile ranges. Continuous variables will be compared using Student’s *t* test or the Mann-Whitney *U* test, as appropriate.

The primary analysis will examine the difference in primary outcome between groups and will be reported as an absolute difference; an unpaired two-tailed t test will be used to test the statistical significance of the mean difference between the three groups. Then, the primary outcome will be analyzed using a linear mixed model adjusted by a set of baseline variables (gender or age) that are strongly believed to affect the outcome. Secondary outcomes will be analyzed using linear, logistic, or ordered regression analysis methods as appropriate, with the same adjustments as the primary outcomes. The primary analysis will be conducted according to the intention-to-treat principle, and per-protocol analysis will be performed and reported separately. All estimated treatment effects will be accompanied by 95% confidence intervals and p-values. Analysis will be performed by use of SPSS statistical package (IBM, version 21.0; SPSS).

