Remimazolam is a water-soluble benzodiazepine intravenous drug, developed for the induction and maintenance of general anesthesia, short-term sedation during various diagnostic and therapeutic procedures as well as long-term sedation during ICU stay. Remimazolam combines the favorable safety profile of benzodiazepines with regard to hemodynamic stability with propofol’s fast onset and offset characteristics and improved controllability. For remimazolam induction of anesthesia, a short infusion of 6 or 12 mg/kg/h was used, and the mean time to LOC (the time when the patient became unresponsive to the shaking of their shoulder) was slightly longer for remimazolam (102 s and 88.7 s for 6 mg/kg/h and 12 mg/kg/h induction doses, respectively) when compared to propofol (78.7 s) in ASA I to II patients in the large phase IIb/III study. There were no occurrences of intraoperative arousal or recall, need for rescue sedative medication, or body movements in any patients [23]. Doi et al. also demonstrated both induction regimens (6 and 12 mg/kg/h) were equally efficacious and safe in vulnerable patients (ASA III); a significantly shorter time to LOC (81.7 s vs 97.2 s) was observed with the higher remimazolam dosage [27]. Considering that morbidly obese patients undergoing general anesthesia are at risk of hypoxemia during anesthesia induction, even after adequate preoxygenation, altered respiratory mechanics and physiology in the obese lead to an apnea time of only 2–4 min [28]. According to the previous study, the time of LOC caused by 12 mg/kg/h is closer to that of propofol, which is more suitable for rapid sequential induction strategy and reducing safe apnea time in obese patients, so in this study, we choose 12 mg/kg/h as the induction dose.

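### The 0.1 mg/kg target behind the 90% power rests on a contrast between infusion rates that does not carry over to an endpoint measured per kilogram of each group's own weight scalar

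*Protocol article*

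**What the plan says.** The Sample size calculation section states: "The sample size calculation is based on the ability to detect a difference of approximately 0.1 mg/kg between groups" in dose per kilogram. As support it cites studies describing a "clinically important difference of 0.12 with a standard deviation of 0.08 of the mean cumulative doses of remimazolam induction to reach LOC", the comparison being "between 6 mg/kg/h and 12 mg/kg/h groups". It concludes: "we calculated a sample size of 20 subjects per group with a power of 90%, alpha 0.025, and a 20% dropout rate".

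Three other parts of the protocol bear on this:

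- **Dosing.** The Abstract and the section Induction of general anesthesia set the induction rate at 12 mg/kg/h in all groups. The kilogram is TBW in the TBW and control groups and LBW in the LBW group.
- **Endpoint.** The section Assessment of primary outcome divides the dose up to MOAA/S 0 by the weight that set the rate: TBW in the TBW and control groups, lean weight in the LBW group.
- **Source times.** The Discussion gives mean times to loss of consciousness in the cited study as "102 s and 88.7 s for 6 mg/kg/h and 12 mg/kg/h induction doses, respectively", with loss of consciousness defined there as "the time when the patient became unresponsive to the shaking of their shoulder". A second cited study, in ASA III patients, gives 97.2 s and 81.7 s for the same two rates.

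On the analysis, "an unpaired two-tailed t test will be used to test the statistical significance of the mean difference between the three groups". Only the obese groups are randomised: "Forty obese patients are randomly allocated in a 1:1 ratio to either the TBW group or the LBW group".

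**The concern.** The supporting figure and the endpoint are different quantities. In the cited comparison the rate per kilogram doubles between groups, so the dose per kilogram differs greatly even though the times to loss of consciousness are close. In this trial the rate per kilogram of the relevant scalar is the same in every group, so dose per kilogram can differ only as far as time differs. A difference produced by unequal rates says nothing direct about an endpoint that cancels the rate.

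TBW versus LBW is the only randomised comparison and it serves the primary objective. If the true difference on this endpoint is well below 0.1 mg/kg, a non-significant result reported beside a 90% power claim could be taken to show that the two scalars are interchangeable.

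**Working it through.** **1. The plan's own figure.** Inputs from the Sample size calculation section: difference 0.1, SD 0.08, alpha 0.025 (taken as two-sided, since the test is two-tailed), power 90%, dropout 20%.

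n = 2 × (2.241 + 1.282)² × 0.08² / 0.1² = 15.9, so 16 per group; 16 / 0.8 = 20. This matches the plan. Power at 16 per group is 90.2% by the normal approximation (87% by the noncentral t). A difference of 0.12 would give 12, then 15, so the calculation uses 0.1 and 0.12 is only its support.

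**2. Where 0.12 comes from.** Dose per kg = rate × seconds / 3600.

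- 12 × 88.7 / 3600 = 0.296 mg/kg
- 6 × 102 / 3600 = 0.170 mg/kg
- Difference 0.126 mg/kg, higher at the faster rate

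The second cited study gives 12 × 81.7 / 3600 − 6 × 97.2 / 3600 = 0.272 − 0.162 = 0.110 mg/kg.

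**3. What this trial's endpoint measures.** At 12 mg per kg of own scalar per hour, the own-scalar dose is 12 / 3600 × seconds = seconds / 300. A difference of 0.1 mg/kg is 30 s.

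**4. How TBW versus LBW relates to the cited contrast.** From the protocol's formulas, LBW/TBW = 9270 / (6680 + 216 × BMI) in men and 9270 / (8780 + 244 × BMI) in women.

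| BMI | Men | Women |
|---|---|---|
| 35 | 0.65 | 0.54 |
| 50 | 0.53 | 0.44 |

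Multiplied by 12, the LBW group receives about 5.3 to 7.8 mg per kg TBW per hour against 12 in the TBW group. That is close to the cited 6-versus-12 contrast.

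**5. The cited contrast on this endpoint.**

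- First study: (102 − 88.7) / 300 = 13.3 / 300 = 0.044 mg/kg
- Second study: (97.2 − 81.7) / 300 = 15.5 / 300 = 0.052 mg/kg

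The group with the lower TBW rate now has the higher value, so the sign reverses. Scaling the time difference linearly with rate gives about 0.03 for men at BMI 35 and about 0.05 for women at BMI 50 (first study). The second study reaches about 0.06 at that upper extreme.

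**6. Power for TBW versus LBW.** SD 0.08, two-sided alpha 0.025, noncentral t.

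| Difference (mg/kg) | 16 per group | 20 per group |
|---|---|---|
| 0.03 | 11% | 14% |
| 0.044 | 23% | 29% |
| 0.052 | 31% | 40% |

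**7. Sensitivity.**

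- *Longer time differences to MOAA/S 0, SD still 0.08 (assumed).* At 1.5 times the cited differences, 20.0 to 23.3 s (0.067 to 0.078 mg/kg), power is 54–80% by the normal approximation (50–76% by noncentral t). At 2 times, 26.6 to 31 s (0.089 to 0.103 mg/kg), it is 81–97% (78–96%).
- *Larger SD (assumed; the documents give only 0.08).* At 0.044 mg/kg, SD 0.10 gives 15–19% and SD 0.12 gives 11–13%. Even at 0.1 mg/kg, SD 0.10 to 0.12 gives 68% to 51% with 16 per group.

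**8. Precision.** At SD 0.08 the half-width of the 95% confidence interval is t × 0.08 × √(2/n) = 0.058 mg/kg at 16 per group and 0.051 at 20. That is about as large as the differences in step 5.

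**The case against.** The strongest reply is that nothing is miscalculated. Power is always conditional on a chosen difference, and 90% is right for 0.1 mg/kg with SD 0.08. This stands, and the point is not an arithmetic error.

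A reader might go further and infer that the trial's true power is 10–40% rather than 90%. The documents do not support that as a fact. The low figures need obese patients to respond per kg TBW as the cited patients did, which is close to what the trial sets out to learn. The weight basis of the cited study is not stated; TBW is inferred from the protocol's remarks on labelled dosing. The cited times are to a lighter endpoint than MOAA/S 0, and the deeper endpoint could lengthen the time difference as well as widen the SD, so the mismatch cuts both ways.

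A reader might also infer that 0.12 is not a clinically important difference. The times show that it matches an observed rate contrast; they cannot show what the source called it.

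A third tempting step is to move the primary contrast to mg per kg TBW or total mg, where 0.126 would have 98–99% power. That power would mostly reflect the rate difference built into the design and would say little about which scalar is appropriate.

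Finally, the study calls itself exploratory, plans 95% confidence intervals for all effects, and has a control group not covered by these power figures. The intervals would make imprecision visible, which limits the harm. None of this supplies a reason for 0.1 mg/kg on the endpoint being tested.

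**Conclusion.** The concern holds as a fault in the effect-size basis. The 0.1 mg/kg target is a 30 s difference on this endpoint. The only evidence offered for it is a contrast between two per-kilogram rates whose time differences are 13.3 and 15.5 s, worth about 0.03 to 0.05 mg/kg here across most of the eligible BMI range examined. The unqualified 90% therefore lacks support for TBW versus LBW.

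How far power falls is conditional. It is roughly 11–40% if the cited dose response, the shoulder-shaking times and the SD of 0.08 all carry over. It is about 54–97% if time differences to MOAA/S 0 are 1.5 to 2 times as long with the SD unchanged, and lower wherever the SD is larger. The mismatch itself does not depend on these assumptions, because it follows from the protocol's dosing rate and endpoint definition.

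**What to change.** Rewrite the sample size paragraph and keep both the enrolment and the own-scalar primary endpoint:

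- Remove the 6-versus-12 mg/kg/h contrast as support for the target.
- State the target on the own-scalar endpoint, with its equivalent in time (0.1 mg/kg = 30 s), and justify it on that scale.
- Replace the single 90% with power over a range of differences, for example 0.03 to 0.10 mg/kg, and a range of SDs. State the assumptions, including the lighter endpoint in the source.
- Say that a non-significant TBW-versus-LBW result will be interpreted through its confidence interval and not as evidence that the scalars are equivalent.

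Total induction dose stays a secondary outcome. The cost is some rewording and a less favourable stated power; no extra patients are needed.

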### Statistical analysis

#### Statistical analysis for primary and secondary outcomes

Baseline clinical and demographic characteristics will be summarized and reported using descriptive statistics. Categorical variables will be reported as numbers and percentages and will be compared using the chi-square test or Fisher’s exact test, as appropriate. The Shapiro-Wilks test will be used to first verify the normality of the continuous variables and will be reported as means and standard deviations or as medians and interquartile ranges. Continuous variables will be compared using Student’s *t* test or the Mann-Whitney *U* test, as appropriate.

The primary analysis will examine the difference in primary outcome between groups and will be reported as an absolute difference; an unpaired two-tailed t test will be used to test the statistical significance of the mean difference between the three groups. Then, the primary outcome will be analyzed using a linear mixed model adjusted by a set of baseline variables (gender or age) that are strongly believed to affect the outcome. Secondary outcomes will be analyzed using linear, logistic, or ordered regression analysis methods as appropriate, with the same adjustments as the primary outcomes. The primary analysis will be conducted according to the intention-to-treat principle, and per-protocol analysis will be performed and reported separately. All estimated treatment effects will be accompanied by 95% confidence intervals and p-values. Analysis will be performed by use of SPSS statistical package (IBM, version 21.0; SPSS).

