### Participants

#### Eligibility criteria

Forty obese patients (18 ≤ age ≤ 65 years, American Society of Anesthesiologists (ASA) grades II to III, BMI ≥ 35 kg/m^2^) are randomized to either TBW or LBW group, while twenty normal-weight control group patients (18 ≤ age ≤ 65 years, ASA I to III, 18.5 kg/m^2^ ≤ BMI < 25 kg/m^2^) receive induction dose based on TBW (Fig. 1), who are scheduled to undergo elective eye, ear, nose, throat surgery under general anesthesia and will be enrolled in this clinical trial.

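### The covariate rule for secondary outcomes leaves the recorded pre-induction value out of the BIS, heart rate and blood pressure comparisons, which gives up precision but does not bias the randomised contrast

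*Protocol article*

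**What the plan says.** Three sections of the protocol article bear on this point.

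- **Statistical analysis for primary and secondary outcomes.** After a t test, the primary outcome is analysed with "a linear mixed model adjusted by a set of baseline variables (gender or age) that are strongly believed to affect the outcome". The rule for the remaining outcomes is "Secondary outcomes will be analyzed using linear, logistic, or ordered regression analysis methods as appropriate, with the same adjustments as the primary outcomes". The same section also plans t tests or Mann-Whitney tests for continuous variables; these use no covariates.
- **Definition of secondary outcomes.** The list includes "the BIS value and hemodynamic variables (HR, BP) at the baseline, MOAA/S zero and 1 min after intubation".
- **Data collection.** "Baseline BIS, HR, SBP, DBP, and MAP are recorded before induction". Further readings follow from MOAA/S zero onwards, including one at 1 min after the airway is secured.

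The article nowhere plans the baseline value as a covariate, a change from baseline, or a repeated-measures model for these variables.

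**The concern.** The primary outcome is a dose per kilogram up to loss of consciousness, so it has no pre-treatment value. A covariate set carried over from it cannot contain one. Heart rate, blood pressure and BIS do have one, and it is a natural covariate for their later readings.

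This is more than a detail left to an unseen analysis plan. The article states which adjustments apply, and its qualifier about appropriateness concerns the type of regression. An analysis plan that followed the sentence would omit the baseline value; one that included it would depart from the protocol.

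At stake are the width of the confidence intervals for the BIS and haemodynamic comparisons and their sensitivity to a chance difference in starting values. The primary outcome and the sample size do not depend on it.

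**Working it through.** **The plan's own figure.** The Sample size calculation section gives a difference of 0.1 mg/kg, SD 0.08, power 90%, alpha 0.025 and 20% dropout. The planned t test is two-tailed.

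n per group = 2 × (z₀.₉₈₇₅ + z₀.₉₀)² × SD² / difference² = 2 × (2.241 + 1.282)² × 0.0064 / 0.01 ≈ 15.9, rounded up to 16. Allowing for dropout, 16 / 0.8 = 20.

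The stated 20 per group is reproduced. It concerns the primary outcome only; no calculation is given for BIS, heart rate or blood pressure.

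**Inputs for this check**

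- 20 per randomised arm: "Forty obese patients are randomly allocated in a 1:1 ratio to either the TBW group or the LBW group". After the planned 20% dropout, 20 × 0.8 = 16.
- r, the correlation between the baseline and post-induction value that remains after age and sex. The documents do not give it, so it is an assumption, shown from 0 to 0.7.

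**Precision.** Relative to a model without baseline, the variance of the group difference is approximately

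V = (1 − r²) × (1 + 1/(2n − 4)),

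where the second factor is the cost of estimating one more covariate. For n = 20 it is 1 + 1/36 = 1.028. Effective n per arm is 20/V. The last column is the difference detectable with 80% power at two-sided 0.05, in SD units: (1.960 + 0.842) × √(2V/20). Without baseline (V = 1) it is 0.89 SD.

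| r (assumed) | V | SE ratio | Effective n per arm | Detectable difference (SD) |
|---|---|---|---|---|
| 0 | 1.028 | 1.01 | 19.5 | 0.90 |
| 0.3 | 0.935 | 0.97 | 21.4 | 0.86 |
| 0.5 | 0.771 | 0.88 | 25.9 | 0.78 |
| 0.7 | 0.524 | 0.72 | 38.2 | 0.64 |

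Break-even is where (1 − r²) × 1.028 = 1, so r² = 1/37 and r ≈ 0.16. With 16 per arm the factor is 1 + 1/28 = 1.036 and break-even is r² = 1/29, r ≈ 0.19. The detectable difference then falls from 0.99 SD to 0.87 SD at r = 0.5 and 0.72 SD at r = 0.7.

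**Chance imbalance.** The SD of the baseline difference between two randomised arms is √(2/20) = 0.32 SD. The chance that it exceeds 0.5 SD in either direction is 2 × [1 − Φ(0.5/0.316)] = 0.11. With 16 per arm the SD is √(2/16) = 0.35 and the chance is 0.16. A baseline difference of d moves the expected unadjusted follow-up difference by about r × d; for example, 0.5 × 0.5 = 0.25 SD at r = 0.5. The stated models leave this in place.

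**The case against.** Several objections limit the point, and most of them stand.

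- **Bias.** A reader might infer that chance baseline differences will be mistaken for drug effects. For TBW versus LBW this goes too far: randomisation makes the estimate without baseline unbiased on average, and its confidence interval already allows for chance imbalance.
- **Baseline ignored.** It is recorded and listed among the secondary outcomes, so an imbalance would be visible when reported. It is only unused in the between-group model.
- **Comparability with controls.** The third group, "while twenty normal-weight control group patients", is not randomised and differs from the obese groups by design in BMI and in permitted ASA grade. Baseline adjustment addresses these systematic differences only in part and does not make the groups comparable.
- **Size.** Quoting only r = 0.5 to 0.7 and the large-sample formula 1/(1 − r²) gives 33% to 96% more patients. With the cost of the covariate it is about 30% to 91%, there is almost no gain at r = 0.3, and there is a small loss at r = 0. For BIS, r may be low: awake values may vary little, and the Maintenance section adjusts the infusion after loss of consciousness to hold BIS between 40 and 60.
- **Importance for the choice of scalar.** A reader might take haemodynamic stability as the main argument for one scalar. The Objectives section rests that choice on the induction dose; the Discussion uses haemodynamic stability to justify the MOAA/S zero endpoint.
- **Choice of model.** A mixed model for a single dose per patient, beside ordinary regressions for repeated readings, may look like two models exchanged. Nothing in the text shows this, and separate regressions at two time points are valid.

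The stated rule itself remains. It fixes the covariates, and no other sentence adds the baseline value.

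**Conclusion.** The point holds as a minor one. As written, the models for post-induction BIS, heart rate and blood pressure exclude the baseline value of the same variable. For the randomised contrast the consequence is lost precision and uncorrected chance imbalance, not bias on average.

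The size of the loss rests wholly on the assumed r. Adjustment does slightly worse than no adjustment below about r = 0.16 and is worth roughly 30% more patients per arm at r = 0.5. The figure of 11% for a baseline imbalance above 0.5 SD needs no assumption about r, only approximate normality of the mean difference and 20 patients per arm. The study calls itself exploratory and only secondary outcomes are touched, so no stronger conclusion is warranted.

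**What to change.** In the section Statistical analysis for primary and secondary outcomes, add a sentence to this effect: BIS, heart rate, SBP, DBP and MAP at MOAA/S zero and at 1 min after intubation are each analysed by linear regression on group, with the pre-induction value of that variable, sex and age as covariates. Name sex and age together as a definite set, because the present wording joins them with an or. A mixed model over these two time points is optional; extending it to the later readings goes beyond the time points that the secondary outcome names.

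State also that comparisons of these variables with the normal-weight group are descriptive.

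The cost is one degree of freedom per model and a change of wording, with no new data and no change to the sample size. The wording should be settled before the outcomes are compared by group.
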